## Abstract

**Background:**

Obesity and asthma have reached epidemic proportions in the US. Their concurrent rise over the last 30 years suggests that they may be connected. Numerous observational studies support a temporally-correct, dose-response relationship between body mass index (BMI) and incident asthma. Weight loss, either induced by surgery or caloric restriction, has been reported to improve asthma symptoms and lung function. Due to methodological shortcomings of previous studies, however, well-controlled trials are needed to investigate the efficacy of weight loss strategies to improve asthma control in obese individuals.

**Methods/Design:**

BE WELL is a 2-arm parallel randomized clinical trial (RCT) of the efficacy of an evidence-based, comprehensive, behavioral weight loss intervention, focusing on diet, physical activity, and behavioral therapy, as adjunct therapy to usual care in the management of asthma in obese adults. Trial participants (n = 324) are patients aged 18 to 70 years who have suboptimally controlled, persistent asthma, BMI between 30.0 and 44.9 kg/m^2^, and who do not have serious comorbidities (e.g., diabetes, heart disease, stroke). The 12-month weight loss intervention to be studied is based on the principles of the highly successful Diabetes Prevention Program lifestyle intervention. Intervention participants will attend 13 weekly group sessions over a four-month period, followed by two monthly individual sessions, and will then receive individualized counseling primarily by phone, at least bi-monthly, for the remainder of the intervention. Follow-up assessment will occur at six and 12 months. The primary outcome variable is the overall score on the Juniper Asthma Control Questionnaire measured at 12 months. Secondary outcomes include lung function, asthma-specific and general quality of life, asthma medication use, asthma-related and total health care utilization. Potential mediators (e.g., weight loss and change in physical activity level and nutrient intake) and moderators (e.g., socio-demographic characteristics and comorbidities) of the intervention effects also will be examined.

**Discussion:**

This RCT holds considerable potential for illuminating the nature of the obesity-asthma relationship and advancing current guidelines for treating obese adults with asthma, which may lead to reduced morbidity and mortality related to the comorbidity of the two disorders.

**Trial registration:**

NCT00901095

## Background

Obesity has been increasingly linked to asthma. Over the last 30 years there has been a rapid, concurrent increase in the prevalence of both chronic diseases in the U.S. and other westernized countries [1,2]. A growing number of prospective studies support a temporally correct, dose-response relationship between body mass index (BMI) and incident asthma in adults and children of multiple nationalities and racial/ethnic groups [3-5]. Obesity also has been shown to alter prevalent asthma towards a more difficult-to-control phenotype [6-11]. Some evidence suggests that selected manifestations of the obesity-asthma relationship may be stronger in females [12-15]. Animal studies support a causal link between the two disorders [16-18], and several mechanisms have been postulated [5,19-21]. However, elucidating the exact nature of the obesity-asthma association in humans remains an area of active research [20].

The National Asthma Education and Prevention Program Expert Panel Report 3 identified obesity as a significant comorbidity and recommended that treatment of obesity be considered in obese adults with asthma [22]. However, this recommendation was, in the Panel's evaluation, based on limited data. The evidence available to date suggests that weight loss, induced by surgery or caloric restriction, is associated with improved asthma symptoms, lung function, medication usage, and quality of life in obese adults with asthma [23-26]. Much of this research, however, suffers from notable methodological inadequacies, which include lack of randomization, small sample size, and short duration, among others. In addition, neither surgery nor caloric restriction alone is the recommended first-line therapy for weight loss; the latter emphasizes a comprehensive approach to lifestyle change, focusing on diet, physical activity, and behavioral self-management [27]. Further research is needed.

## Aims

The BE WELL (*B*reathe *E*asier through *We*ight *L*oss *L*ifestyle) intervention trial was designed to address the gap in knowledge of whether weight loss improves asthma control. It aims to evaluate the efficacy of an evidence-based, comprehensive weight loss lifestyle intervention as adjunct therapy to usual care in the management of asthma in obese adults. The primary hypothesis is that compared with participants in the usual care (UC) arm, those in the weight loss intervention (WL) arm will achieve greater improvement in asthma control, as measured by a validated composite measure, the Juniper Asthma Control Questionnaire (ACQ) [28], at 12 months follow-up. Secondary aims include comparing the WL and UC arms on changes in ACQ scores at six months and in lung function, asthma-specific quality of life (QoL), asthma medication use, and asthma-related health care utilization (HCU) at six and 12 months. Potential mediators (e.g. weight loss and change in physical activity level and diet composition) and moderators (e.g., socio-demographic characteristics and comorbidities) of the intervention effects will be explored.

## Methods/Design

### Study Design

BE WELL is a two-arm randomized controlled clinical trial (RCT) in which obese patients ages 18-70 years with suboptimally controlled, persistent asthma (n = 324) will be equally randomized to the WL or UC arm. All procedures and materials were approved by the Kaiser Foundation Research Institute's Institutional Review Board.

### Eligibility Criteria

Participants will be recruited from multiple medical centers of Kaiser Permanente in Northern California (KPNC). Patients ages 18-70 years who are obese and have suboptimally controlled, persistent asthma will be eligible to participate. Table 1 enumerates the inclusion and exclusion criteria. Exclusion criteria were designed to ensure each participant's ability and safety to complete the study requirements, minimize error associated with primary outcome, and prevent possible missing data. Individuals of both genders and any racial or ethnic background who speak English, meet the inclusion criteria, and have no exclusion criteria will be eligible. Based on the demographics of obese asthma patients at the selected KPNC sites, the gender and ethnic distributions of the target enrollment population are expected to consist of 67% women, 57% White, 27% Black, 7% Hispanic/Latino, and 9% Asian/Pacific Islander.

**Table 1 T1:** Participant inclusion and exclusion criteria

Inclusion criteria
* Age (as of date of enrollment)
- Lower age limit: 18 years
- Upper age limit: 70 years
* Gender: Both men and women
* Race/ethnicity: All racial and ethnic groups
* Body mass index 30.0-44.9 kg/m^2^
* Suboptimally controlled asthma:
- Documented diagnosis of asthma on the current medical problem list
- Currently prescribed an anti-asthma medication
- Score <20 on the Asthma Control Test [75]
- Demonstrable airway reversibility
* Kaiser member for ≥ 1 year
* Able and willing to enroll and provide written, informed consent, i.e., to: 1) meet the time and data collection requirements of the study; 2) be randomized to one of the two intervention arms; 3) adhere to the recommendations of the study intervention as assigned; 4) participate in follow-up for 12 months; and 5) allow extraction of relevant information from their medical records.
Exclusion criteria
* Inability to speak, read or understand English;
* Intermittent asthma, defined as either seasonal asthma or (daytime asthma symptoms <2×/week and nocturnal symptoms <2×/month and no use of controller medications);
* Diagnosis of COPD (emphysema or chronic bronchitis) suggested by patient report of doctor diagnosis, spirometry, and smoking history;
* Use of weight-loss medications in the past 3 months;
* Initiation or change of antidepressant medication within the past 3 months;
* Regular use (>5 days/month) of the following medications: oral corticosteroids, insulin, oral hypoglycemics, anti-psychotics, and mood stabilizers;
* Currently enrolled in a group or individual intervention program that overtly aimed at weight loss, nutrition and/or physical activity at Kaiser or elsewhere;
* Planning to undergo bariatric surgery during the study period;
* Inability to perform pulmonary function tests by spirometry in a consistent manner;
* Having a medical or physical condition that makes moderate intensity physical activity (like a brisk walk) difficult or unsafe;
* Significant medical co-morbidities, including uncontrolled metabolic disorders (e.g., thyroid, renal, liver), diabetes, heart disease, stroke, and ongoing substance abuse;
* Hospitalization for psychological or emotional problems within the past two years;
* Diagnosis of cancer (other than non-melanoma skin cancer) that is/was active or treated with radiation or chemotherapy within the past 2 years;
* Diagnosis of a terminal illness and/or in hospice care;
* Currently pregnant, lactating, or planning to become pregnant during the study period;
* Already enrolled or planning to enroll in a research study that would limit full participation in the study or confound the interpretation of the study's findings;
* Family/household member of another study participant or of a study staff member;
* No longer a Kaiser patient or planning to transfer care outside of Kaiser during the study period;
* PCP determination that the study is inappropriate or unsafe for the patient;
* Investigator discretion for clinical safety or protocol adherence reasons.

### Recruitment and Screening Process

The target sample size for BE WELL is 324, to be recruited in five sequential cohorts. Recruitment for each cohort will begin by querying KPNC's electronic asthma registry to identify obese adult patients who are likely to have suboptimally controlled, persistent asthma based on them past ER visits, hospitalizations, and/or medication dispensing records. These patients will be reviewed by their primary care provider (PCP) to determine whether their participation in the study is medically appropriate and safe. Patients for whom PCP approval is obtained will be invited by mail to participate in the study and be asked to complete, either online or by phone, a brief eligibility screening questionnaire pertaining primarily to major exclusions that patients can reliably answer on their own (e.g., pregnancy, plans to move, active cancer). Patients who pass the initial screen will be scheduled for a formal in-person eligibility determination visit (BV1) and, if eligible, a second visit (BV2) to complete baseline data collection prior to randomization.

BV1 will occur no more than four months after the initial screen, and no more than two months prior to BV2. Written informed consent will be obtained, followed by completion of additional eligibility questionnaires, including screening for angina, peripheral vascular disease (PVD), and severe depression. Height and weight will be measured and BMI calculated. Patients whose BMI is in the eligibility range between 30.0-44.9 kg/m^2 ^will have spirometry performed before and after administration of a short-acting beta agonist to determine reversibility of airway obstruction. Patients with very poor lung function (pre-bronchodilator forced expiratory volume in one second [FEV1]<40% of predicted or post-bronchodilator FEV1<50% of predicted) or who have possible angina, PVD, or severe depression will be referred to a study physician and their PCP for evaluation and may only continue in the study with explicit physician authorization. Participants who prove fully eligible will be given instructions, a two-week asthma diary form, and a three-day food record form to be completed and returned at BV2.

BV2 will occur at least two weeks after BV1 to allow time for participants to complete the asthma diary and food record. Also, BV2 will occur no more than four weeks prior to the start of the intervention. It will involve review of the patient's two-week asthma diary and three-day food record, completion of the baseline questionnaire, measurement of weight, waist circumference, hip circumference, blood pressure, and pre-bronchodilator spirometry.

### Randomization and Blinding

Following BV2, participants will be randomized in a 1:1 ratio to the WL or UC arm. By applying a balance algorithm that originated in cluster randomized trials [29], BE WELL randomization will assure very close balance at baseline on age, sex, race/ethnicity, BMI and ACQ score stratified by participating KPNC medical centers, and better than chance balance on characteristics correlated with the balancing variables. Within each medical center, participants will be randomized in blocks to take advantage of complete data on baseline covariates across the recruited sample prior to randomization.

For the first block within a medical center, the imbalance scores of all possible allocations with equal numbers of participants between two anonymous groups (1 and 2) will be calculated using equation 1. The correspondence of groups 1 and 2 with either the WL or UC arm will be assigned randomly at the outset and used consistently throughout the trial.(1)

where k is the kth balancing factor (k = 1 to 5) as listed above;  and  are the average of kth factor for groups 1 and 2, respectively; and the weights (w) determine the relative contribution of each balancing factor to the imbalance B [30]. In BE WELL, equal weights will be assumed for all balancing factors. For categorical factors, orthogonal dummy variables, which identify individual factor levels, will be coded before imbalance score calculation. A set of optimal allocations will be determined by the lowest 1,000 calculated B values [30]. One allocation will be randomly selected from the set of optimal allocations for the block of participants about to be randomized.

After randomization of the first block of participants within a medical center, allocations for each subsequent block will be conditional on the chosen allocations of participants in earlier blocks. The imbalance score B for a new block will be computed using equation 2.(2)

where n_1 _is the number of participants in the existing block(s) and n_2 _is the total number of participants with the addition of the new block; *x*_1*ik *_and *x*_2*ik *_represent the kth factor of ith participant allocated in group 1 or 2. The process of sampling from the 1,000 lowest calculated B values will be repeated for all subsequent blocks.

This randomization procedure not only minimizes imbalance for the chosen baseline covariates between treatment groups and correlated characteristics, but also ensures concealment of treatment allocation, with recruitment staff completely unable to influence allocation. A designated research staff member who is not involved in follow-up data collection or data analysis will carry out randomization using a computerized program. Anonymous labels of treatment assignments will be used in all study reports and other materials to ensure blinding of the investigators and staff responsible for follow-up data collection and data analysis. Staff responsible for delivering the WL intervention will be masked to all outcome data until the end of trial. Due to the nature of this intervention, blinding of the participants is not feasible.

### Baseline and Follow-up Measures and Data Collection

Table 2 shows the study measures and data collection schedule. In addition to the screening and baseline data collection activities described previously, follow-up visits for questionnaires, clinical measurements, and adverse event monitoring will be conducted at six and 12 months after randomization.

**Table 2 T2:** List of measures and data collection schedule

	Baseline	Follow-up month	
		
		6	12
**Questionnaires**			
Juniper Asthma Control Questionnaire (ACQ)	X	X	X
Juniper Mini Asthma-specific Quality of Life Questionnaire (mini-AQLQ)	X	X	X
Two-week asthma symptom diary	X	X	X
Baseline Dyspnea Index	X		
Transition Dyspnea Index		X	X
Three-day food record	X	X	X
Eating Habits Confidence Survey	X	X	X
Social Support and Eating Habits Survey	X	X	X
Stanford Seven-day Physical Activity Recall	X	X	X
Exercise Confidence Survey	X	X	X
Total number of steps in the past seven days (per pedometer reading)	X	X	X
Social Support and Exercise Survey	X	X	X
Rose questionnaire for angina and peripheral vascular disease	X	X	X
Center for Epidemiologic Studies Depression Scale (CES-D)	X	X	X
Depression Anxiety Stress Scale	X	X	X
Obesity Related Problems Scale	X	X	X
12-item Short Form Health Survey (SF-12)	X	X	X
Berlin Questionnaire for Sleep Apnea	X	X	X
Gastroesophageal Reflux Disease Symptom Assessment Scale	X	X	X
Adverse events	X	X	X
Care at non-Kaiser health care facilities	X	X	X
Demographics	X		
**Clinical Measures**			
Height	X		
Weight, waist circumference, hip circumference, waist to hip ratio (WHR)	X	X	X
Blood pressure	X	X	X
Spirometry: Forced maneuver - FEV1, FEV6, FVC (absolute and % predicted values), FEV1/FVC, FEV1/FEV6; Slow maneuver - VT, ERV, IC, VCin, VCex	X	X	X
**Data from KPNC Electronic Databases**			
Current medical problems	X		X
Medications currently prescribed	X	X	X
Medications dispensed^2^	X		X
Health care utilization^2^	X		X
Primary care provider characteristics	X		X
**Recruitment and intervention process measures (monitored continuously)**			
**Safety of participants in the intervention arm (monitored continuously)**			

^1^Pre- and post-bronchodilator spirometry will be obtained at baseline visit 1 to determine reversibility of airway obstruction, which is an eligibility criterion. Only pre-bronchodilator spirometry will be performed at baseline visit 2 and at 6- and 12-month assessments and the measurements obtained will be used for analysis.

^2^Data will be extracted for a period of 12 months before and after randomization.

Abbreviations: ERV, expiratory reserve volume; FEV1, forced expiratory volume in one second; FEV6, forced expiratory volume in six seconds; FVC, forced vital capacity; IC, inspiratory capacity; KPNC, Kaiser Permanente in Northern California; VCin and VCex, inspiratory and expiratory vital capacity; VT, tidal volume.

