#### Statistical analysis

The primary hypothesis compares Juniper ACQ scores between the WL and UC arms at 12 months using an intent-to-treat analysis. Linear mixed modeling, using SAS PROC MIXED [67] will test time and group interactions to assess whether within-subject change in Juniper ACQ scores differs by condition (equation 3).(3)

Due to randomization, the distributions of baseline values on the dependent variable (Y_0_) and baseline covariates (X_i _where i = 1 to k) should be similar between treatment arms and thus not bias the analysis. Nonetheless, to the extent they are associated with the outcome, their inclusion in the model will account for otherwise unexplained variation and hence increase the efficiency of the analysis. In addition, their inclusion will guard against imbalance in the distributions of these covariates between treatment arms, which can still occur despite randomization. a, g, and δ represent the random effects caused by clustering of patients with physicians and, in turn, physicians within clinics, and by blocking of patients within medical centers. ε takes into account the correlation of repeated measures within subjects.

The same analysis strategy is appropriate for evaluating secondary aims where the hypotheses are identical but with different outcome measures (e.g., lung function, asthma-specific QoL, asthma-related HCU). The longitudinal effects of the intervention will be assessed using the same model, except that the focus is comparisons within the intervention arm at different time points. Analyses will also be conducted to examine whether there is a dose-response relationship between intervention adherence and outcome, where dose is defined in terms of number of group sessions attended, number of self-monitoring logs kept, average daily intakes of calories and fat, and average number of minutes of physical activity per week.

The primary analyses will be intention-to-treat. Secondary per-protocol or as-treated analyses will be performed to help elucidate the primary findings. For subjects with missing data at follow-up, we will conduct and report on sensitivity analyses in which several previously recommended approaches for handling missing data in longitudinal trials will be used, e.g., multiple imputation and the pattern-mixture model [68].

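### The screening-visit pre-bronchodilator spirometry has no stated role in the lung-function analysis; adding it as a separate baseline covariate is a small, nearly free gain in precision

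*Protocol article*

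**What the plan says.** Under Recruitment and Screening Process, patients with a BMI in range attend BV1 and "will have spirometry performed before and after administration of a short-acting beta agonist to determine reversibility of airway obstruction". At BV2 the list of measurements includes "measurement of weight, waist circumference, hip circumference, blood pressure, and pre-bronchodilator spirometry". The interval is bounded on both sides: "BV2 will occur at least two weeks after BV1", and BV1 is "no more than two months prior to BV2". Randomization follows BV2 (Randomization and Blinding).

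Footnote 1 to Table 2 gives the two visits different roles. For BV1: "Pre- and post-bronchodilator spirometry will be obtained at baseline visit 1 to determine reversibility of airway obstruction, which is an eligibility criterion". For the later visits, pre-bronchodilator spirometry alone is "performed at baseline visit 2 and at 6- and 12-month assessments and the measurements obtained will be used for analysis".

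The Statistical analysis section fits a linear mixed model that adjusts for the baseline value of the outcome and for baseline covariates, on the ground that "to the extent they are associated with the outcome, their inclusion in the model will account for otherwise unexplained variation". It applies the same strategy to the secondary outcomes, lung function among them.

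**The concern.** Reversibility is an inclusion criterion, so everyone who is randomized has a pre-bronchodilator reading from BV1 and a second one from BV2. A single reading carries visit-to-visit noise, and that noise weakens it as a baseline covariate. A second reading taken before randomization can recover part of the loss. By the plan's own argument for covariate adjustment it is a natural candidate, yet the article gives it no analytic role and no reason for leaving it out.

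What is at stake is the width of the confidence intervals for the between-arm spirometry comparisons. These have some weight here: participants cannot be blinded, and spirometry is an objective measurement beside a primary outcome that is largely self-reported.

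**Working it through.** **The plan's own figure.** The article states no precision or power for lung function. Its sample size is for an effect size of 0.4 with 90% power at two-sided 5%. The normal approximation gives 2 × (1.960 + 1.282)² / 0.4² = 131.4, so 132 per arm and 264 in all, or 264 / 0.8 = 330 after 20% loss. With the stated 259 completers, power is 89.6% (89.4% by the exact t). This is close enough to the stated 324 and 90%. The calculation is a plain t-test that credits no baseline adjustment, so nothing below alters it.

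**Inputs for the gain.** From the article: two pre-randomization readings, two weeks to two months apart, and a baseline-adjusted model. Not in the article: the correlations between visits. These are assumptions, shown over a range.

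**Case A: BV1 and BV2 predict month 12 equally well.** Let *rel* be the correlation between two readings close in time and *stab* the 12-month correlation of the underlying value.
- BV2 only: r = rel × stab.
- Both readings: r = rel × stab / √((1 + rel)/2). With equal predictive value, two separate covariates and their mean give the same fit.
- Residual variance is 1 − r².

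| rel | stab | r, BV2 only | r, both | variance ratio | SE reduction |
|---|---|---|---|---|---|
| 0.80 | 0.95 | 0.760 | 0.801 | 0.848 | 8% |
| 0.90 | 0.90 | 0.810 | 0.831 | 0.900 | 5% |
| 0.95 | 0.85 | 0.807 | 0.818 | 0.952 | 2% |

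The other two corners of these ranges lie inside the same band: 0.904 at 0.80/0.85 and 0.887 at 0.95/0.95.

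**Case B: BV1, being earlier, predicts month 12 less well.** Write b for the BV1–BV2 correlation, r2 for BV2–month 12 and r1 for BV1–month 12.
- Two covariates: R² = (r1² + r2² − 2·b·r1·r2) / (1 − b²).
- Simple mean: R² = (r1 + r2)² / (2(1 + b)).
- Each is compared with BV2 alone, whose residual variance is 1 − r2².

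| b | r2 | r1 | ratio, separate covariates | ratio, simple mean |
|---|---|---|---|---|
| 0.90 | 0.80 | 0.80 | 0.906 | 0.906 |
| 0.90 | 0.80 | 0.77 | 0.963 | 0.976 |
| 0.90 | 0.80 | 0.75 | 0.987 | 1.022 |
| 0.90 | 0.80 | 0.72 | 1.000 | 1.089 |

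In the last row r1 = b × r2 (0.90 × 0.80 = 0.72), so BV1 carries nothing beyond BV2 and the gain is nil. The simple mean is then worse than BV2 alone. Separate covariates do no harm beyond the lost degree of freedom, roughly 1/259 ≈ 0.4% of variance.

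**A more favourable model, not relied on.** If all three visits share one correlation r, the ratio is (1 + 2r)/(1 + r)², a gain of 11% at r = 0.5 and 22% at r = 0.9. This needs readings weeks apart to be no more alike than readings a year apart.

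**Selection at BV1.** A simulation with an assumed mean FEV1 of 2.5 L, SD 0.7 L and a 12% reversibility threshold gave mean BV1 values of 2.21 L against 2.51 L at BV2 (r = 0.7), and 2.31 against 2.49 L (r = 0.9). Regression to the mean of this kind would distort within-arm change measured from BV1. Adding BV1 as a covariate still lowered the residual variance in each case run.

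**The case against.** The strongest reply is that nothing here is wrong. One post-screening baseline per outcome is ordinary practice. BV2 is closer to randomization, is collected with the other baseline measures, and is free of the day-specific selection that the reversibility criterion imposes at BV1. The Statistical analysis section also plans within-arm comparisons over time, which a baseline contaminated by BV1 would distort. Much of this stands: it justifies BV2 as the reported baseline and for within-arm change. It does not count against BV1 as an extra covariate in the between-arm model, because the selection precedes randomization and affects both arms alike.

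A second reply is that the footnote excludes BV1 only by implication, and that the model carries an unlisted set of baseline covariates which a fuller plan might define. That is fair as far as it goes. Still, the article does say which spirometry readings are for analysis and gives BV1 a different purpose, so the natural reading is that BV1 has no place in the model.

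A third reply concerns size: the gain rests on correlations that the article does not report. That stands, and it is why the range starts at zero.

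**Conclusion.** The point holds as a minor efficiency suggestion for secondary outcomes. With the BV1 value added as a separate covariate, the residual variance of the between-arm forced-spirometry comparisons falls by about 0 to 15% and the standard error by about 0 to 8%. The upper end assumes that BV1 and BV2 predict month 12 equally well; the lower end applies if BV1 adds little beyond BV2.

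A reader might infer more than the documents support:
- *That the planned analysis is biased.* It is not. The BV2-only comparison is valid.
- *That the trial's power is affected.* The 324 and 259 belong to the primary asthma control score, and that calculation uses no baseline spirometry. Restating the gain as extra completers out of 259 would borrow a figure from an outcome on which this point does not bear.
- *That a gain is assured.* With modest decay in the BV1 correlation it is about 4%, and it can be nil.
- *That all spirometry measures benefit.* The article does not say that the slow-maneuver volumes are measured at BV1, so they are covered only if they were obtained there.

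**What to change.** Keep BV2 as the reported baseline and as the reference for within-arm change. In footnote 1 and the analysis plan, add one sentence: the BV1 pre-bronchodilator value enters as a separate covariate, beside the BV2 value and not averaged with it, in the between-arm models for forced-spirometry measures such as FEV1 and FVC. Extend this to slow-maneuver measures only if they were obtained at BV1. Fix the wording before unblinding.

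The cost is one degree of freedom per model. No new data, visits or participants are needed, and the primary analysis and its sample size stay as they are.
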